### Participant timeline

Eligible participants will be enrolled from January, 2023 to December, 2024. During the 28-day screening period, baseline information on demographics, number of monthly headache days, number of monthly acute medication intake days, headache intensity, and sum scores of HIT-6 and SF-36 for the past 4 weeks before randomization will be collected through a patient's headache diary or face to face interview in outpatient clinic. Education on medication overuse using BI strategy (36) will be finished before randomization (Visit 0). Training on the eDiary will be started after a signed consent form obtained from a study participant and prior to the first administration of study intervention. At each visit during the double-blind phase and follow-up (Visit 1–4), outcomes and adverse events will be evaluated correspondingly. Schedule of enrollment, interventions, and assessments following SPIRIT 2013 statement (42) is provided in Table 1.

**Table 1 T1:** SPIRIT flow diagram of enrollment, interventions, and assessments.

**Time point**	**Study period**					
	**Baseline screening**	**Allocation**	**Double-blind treatment period**			**Follow-up**
	**Day-28–0**	**Day 0**	**Week 4 (**±**3 day)**	**Week 8 (**±**3 day)**	**Week 12 (**±**3 day)**	**Week 24 (**±**3 day)**
**Enrollment**						
Eligibility screening	x					
Informed consent	x					
eDiary training	x					
Allocation		x				
BI education	x					
**Interventions**						
Gastrodin			♦———————————————————————–♦			
Placebo			♦———————————————————————–♦			
**Assessments**						
Demographic information	x					
Monthly headache days	x		x	x	x	x
Month medication intake days	x		x	x	x	x
Headache intensity	x		x	x	x	x
Moderate or severe headache days	x		x	x	x	x
Headache Impact Test-6	x		x	x	x	x
Short Form 36-Item Health Survey	x		x	x	x	x
Drop-outs			x	x	x	
Adverse events			x	x	x	

### Sample size

We will estimate each of the above mentioned variables to calculate endpoints for MOH studies according to a published study (22). Hypothesis test will be 2-tailed with 90% power and a significance level of *P* < 0.05. Sample size estimations for the four recommended endpoints are provided in Table 2.

**Table 2 T2:** Sample sizes estimation for each critical endpoint.

**Endpoints**	**Target power**	**Alpha**	**N1**	**N2**	**N**	**Assumed proportion (or mean) for treatment group**	**Referred proportion (or mean ±SD) for control group^*^**	**Difference between groups**
Reduction in monthly headache days	90%	0.05	77	77	154	46%	22%	24%
Cured medication overuse headache	90%	0.05	44	44	88	90%	62%	28%
Headache intensity	90%	0.05	22	22	44	20.7	38.4 ± 17.4	17.7

* Data referred for sample size estimation are all obtained from a published study (reference 16) which enrolled patients with medication overused headache who were assigned to restricted acute medication intake group (allowing to take up to 2 days a week with analgesics or migraine medication during the study period).

Finally, we assume group sample sizes of 77 in gastrodin group and 77 in the control group will achieve 90.188% power to detect a difference between the group proportions of 24%. The proportion in the gastrodin group is assumed to be 22% under the null hypothesis and 46% under the alternative hypothesis. The proportion in control group is 22% based on previously published literature (22). The test statistic used is the two-sided *Z*-Test with unpooled variance. To allow for 20% dropouts, we will include 186 patients, corresponding to 93 in each group.

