**Methods:**

A multicenter, randomized, double-blind, parallel, placebo-controlled trial will be performed. A target sample size of 186 patients who fulfill the International Classification of Headache Disorders 3rd version (ICHD-3) criteria for MOH will be recruited and screened during a baseline screening period of 28 days before being randomly assigned to either the gastrodin or placebo group at a ratio of 1:1. Enrolled patients will be assessed for each 4 weeks during the 12-weeks double-blind phase and followed up at week 24. The primary endpoint is mean change in monthly headache day frequency. Secondary endpoints will be the proportion of remitted MOH, change in headache pain intensity, headache impact test (HIT-6) score, 50% responder rate, treatment failure, monthly acute medication intake days, and Short Form 36-Item Health Survey (SF-36) score. Tolerability will be assessed by drop-out rates though safety monitoring during treatment.

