### Outcome measures

As there is a lack of guidelines for reporting results from clinical trials on MOH, we will adopt Hagen et al.'s suggestion on endpoints for MOH studies in follow-up including headache days/month, acute medication use days/month, headache intensity, cured MOH, and responder rate (37).

Primary efficacy endpoint is reduction in the mean number of monthly headache days from baseline at 24-week follow-up.

Secondary efficacy endpoints include:

a. Headache intensity at 12 and 24-week follow-up. The headache intensity at each headache onset will be measured on a 4-point scale (0 = pain, 1 = mild pain, 2 = moderate pain, 3 = severe pain), and be calculated as the average of headache intensity at each headache onset for 1 month;b. Proportion of cured MOH, defined as a patient does not fulfill the diagnostic criteria for MOH in ICHD-3 at 12 and 24-week follow-up;c. Mean change from baseline in total HIT-6 score and the proportion of patients with a ≥ 5-point reduction in total HIT-6 score (38) at 12 and 24-week follow-up. For total HIT-6 scores, a between-treatment group minimally important difference (MID) has been established as ≥2.3 (39). Additionally, a clinically meaningful change for an individual patient has been defined as a ≥ 5-point decrease in total HIT-6 score;d. 50% responder rate, defined as 50% reduction of from baseline in number of moderate or severe headache days at 12- and 24-week follow-up;e. Treatment failure, defined as use of acute medication intake >2 days per week during 12-week treatment;f. Reduction in the mean number of monthly medication intake days for treatment failures at 12- and 24-week follow-up;g. Quality of life (QoL), as measure by the Short Form 36-Item Health Survey (SF-36) (40) at 12- and 24-week follow-up.

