### Statistical methods

All analyses on efficacy endpoints will be performed using the intention-to-treat (43) principle which includes all randomized patients who had an evaluable baseline period of eDiary data (week-0), received at least 1 dose of gastrodin or placebo, and had at least one evaluable follow-up appointment. Safety evaluations will be performed consisting of all participants who received at least 1 dose of study intervention.

Continuous variables are presented as mean ± standard deviation (44) conforming to the normal distribution and median (interquartile range; IQR) for the skew distribution data. Student's *t*-test and Mann-Whitney *U*-test will be used to test differences in continuous variables where appropriate. Categorical variables will be expressed by the number and percentage of occurrences. Differences between two groups will be compared using chi-squared tests or Fisher's exact test where appropriate.

Cox proportional hazard regression (backward stepwise method) analysis and the Kaplan-Meier survival curve will be performed when necessary.

To more completely understand the clinical meaningfulness of the new therapy for MOH results from different headache type, we will conduct a subgroup analysis based on prior headache type (CM/CTTH or CM/ other types of headaches) for all the efficacy endpoints.

Participants who do not complete or are lost to follow-up will be coded as treatment failure, missing values will be handled using multiple imputation method under the missing-at-random (MAR) assumption (45).

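### The sample size and its 90.188% power come from a comparison of two proportions, but the primary endpoint is a mean change in monthly headache days, so power for the primary analysis is not stated

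*Protocol article*

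**What the plan says.** The endpoint is defined twice, each time as a continuous quantity. The Abstract states: "The primary endpoint is mean change in monthly headache day frequency". The Outcome measures section states: "Primary efficacy endpoint is reduction in the mean number of monthly headache days from baseline at 24-week follow-up".

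The Statistical methods section names no test for the primary endpoint specifically. It gives a general rule: Student's t-test and the Mann-Whitney U-test "will be used to test differences in continuous variables where appropriate". Categorical variables follow a separate rule: "Differences between two groups will be compared using chi-squared tests or Fisher's exact test where appropriate".

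The Sample size section sets the design values: "Hypothesis test will be 2-tailed with 90% power and a significance level of" 0.05. In Table 2, the row for the reduction in monthly headache days carries 46% for treatment, 22% for control and 77 per arm. The text below the table treats these values as group proportions, names a two-sided Z-test with unpooled variance, and says that 77 per arm "will achieve 90.188% power to detect a difference between the group proportions of 24" percent. The 77 per arm is then raised to 93 per arm, 186 in total, to allow for dropouts.

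**The concern.** A power figure is valid only for the endpoint, effect measure and test for which it was computed. For two proportions, the variance follows from the proportions themselves through p(1−p). For a mean change it does not: a difference in days and the SD of the change are both needed. The protocol gives neither for headache days.

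The headache-days row has the largest sample size in Table 2, and the text carries only that row forward to 186. The trial's enrolment target therefore rests on a quantity that is not the primary endpoint. The reader is also not told what difference in headache days the trial was designed to detect.

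**Working it through.** **Inputs from the protocol.** Sample size section and Table 2: 46% and 22%, 77 per arm, two-sided alpha 0.05, target power 90%, unpooled Z-test. Outcome measures: continuous primary endpoint. Statistical methods: t-test or Mann-Whitney U-test for continuous variables.

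**Inputs assumed here because the protocol gives none.** A between-group difference of 3 headache days per month; an SD of change of 5 to 10 days; an SD of percentage reduction of 30 to 60 points. They show the range and are not estimates for this trial.

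**Step 1: reproduce the stated figure.** Power = Φ( |p1−p2| / √{[p1(1−p1)+p2(1−p2)]/n} − 1.960 ).

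- Variance sum: 0.46×0.54 + 0.22×0.78 = 0.2484 + 0.1716 = 0.4200.
- Standard error: √(0.4200/77) = 0.0739.
- 0.24/0.0739 = 3.250; 3.250 − 1.960 = 1.290; Φ(1.290) = 90.14%. The protocol states 90.188%.
- Required n: (1.960+1.282)² × 0.4200/0.24² = 76.6, so 77 per arm.

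The stated figure is therefore a two-proportion result and is right as such.

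**Step 2: can 46% and 22% be read so that the figure fits the primary endpoint?**

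- *As responder proportions.* The powered quantity is then binary and is not the primary endpoint. The one responder endpoint on headache days is secondary and counts only moderate or severe headache days.
- *As mean percentage reductions.* The variance p(1−p) is then wrong. It amounts to assuming an SD of √(0.4200/2) = 0.458, about 46 percentage points, which nothing in the protocol supports. A t-test for a 24-point difference with 77 per arm has power 99.9%, 96%, 91%, 84% or 69% at assumed SDs of 30, 40, 45, 50 or 60 points.

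**Step 3: what 77 per arm gives for a mean change.** Normal approximation: detectable standardised difference at 90% power = (1.960+1.282) × √(2/77) = 0.522. With the t distribution it is 0.526.

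| Assumed SD of change (days) | Difference detectable at 90% power, 0.526×SD (days) | Power for an assumed 3-day difference (t-test) | n per arm for 90% power at 3 days (normal approximation) |
|---|---|---|---|
| 5 | 2.6 | 96% | 59 |
| 6 | 3.2 | 87% | 85 |
| 8 | 4.2 | 64% | 150 |
| 10 | 5.3 | 46% | 234 |

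**Step 4: direction.** Suppose that 46% and 22% were the shares of patients passing one common cut-off on a normally distributed change with equal SDs. The implied shift is −0.100 − (−0.772) = 0.672 SD, and comparing the means with 77 per arm would have about 98.6% power (normal approximation). The protocol does not state these conditions, but the example shows that the true power could well exceed 90%.

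**The case against.** The strongest defence is that the calculation is correct in itself, that the row bears the name of the primary endpoint, and that a journal article condenses the full protocol. The first part stands: this is a mismatch between the powered endpoint and the primary endpoint, not an arithmetic error. Condensed reporting does not explain it, because the article states the hypotheses, the test statistic and the variance form in full, all for proportions. The same Table 2 also sizes headache intensity from a mean and SD (38.4 ± 17.4, difference 17.7). A separate analysis plan could not make a two-proportion power apply to a mean change.

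It is also fair to say that the t-test or Mann-Whitney test for the primary endpoint is inferred from a general rule. The inference is reasonable, since the endpoint is continuous in both definitions.

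A reader might go further in four ways that the document does not support:

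- *The trial is underpowered.* Not shown. The 3-day difference and all the SDs above are assumptions, and power falls on either side of 90% within a modest range.
- *A null result could not be interpreted.* Not so. It would be read from the estimate and its confidence interval, whatever the planning assumption was.
- *46% against 22% is really the secondary responder endpoint.* Nothing shows this. That endpoint counts moderate or severe headache days, while the Table 2 row concerns monthly headache days.
- *The sample size can stay as it is, or must rise.* Neither can be asserted without a target difference and an SD.

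**Conclusion.** The point holds as an endpoint and sample-size mismatch. The 90.188% power and the 77 per arm belong to a two-proportion Z-test, and neither reading of 46% and 22% carries them over to a mean change in monthly headache days. Power for the primary analysis is unknown and may be higher or lower than stated.

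The firm result is that 77 per arm gives 90% power for a standardised difference of 0.526, assuming a two-sample t-test, a common SD and 77 evaluable patients per arm. Any figure in days depends on an SD that the protocol does not give. The statement is wrong as written and should be corrected, because it is the sole basis for the enrolment target.

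**What to change.** Remove the 90.188% claim for the primary endpoint, then do one of the following.

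- **(a) Power the primary endpoint as defined.** State an assumed between-group difference in mean change in monthly headache days at week 24 and the SD of that change, each with its source. Restate the power for the planned sample size under the planned test, or state the detectable difference (about 0.53 SD at 90% power with 77 per arm). Whether 186 is still adequate can be judged only after this.
- **(b) If 46% against 22% is a responder proportion, define it explicitly** (which days, which reduction, which time point) and label the Table 2 row as the endpoint it belongs to. Do not equate it with the secondary responder endpoint on moderate or severe headache days unless that is what the source measured. The primary endpoint would still need its own statement under (a).

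In either case, settle which source supplied the control value: the text cites reference 22, the Table 2 footnote reference 16.

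The cost is a rewritten sample-size paragraph and one table row. The stated power may change in either direction.

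### The 20% dropout allowance is too small: 186 patients less 20% leaves about 74 per arm, not the 77 on which the stated 90% power rests

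*Protocol article*

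**What the plan says.** All the inputs are in the Sample size section of the protocol article. The design target is given as "Hypothesis test will be 2-tailed with 90% power and a significance level of *P* < 0.05". The base sample size follows: "group sample sizes of 77 in gastrodin group and 77 in the control group will achieve 90.188% power". The assumed rates are given by "The proportion in the gastrodin group is assumed to be 22% under the null hypothesis and 46% under the alternative hypothesis" and by a control rate of 22% taken from a cited study. The method is named: "The test statistic used is the two-sided *Z*-Test with unpooled variance". The dropout step is a single sentence, "To allow for 20% dropouts, we will include 186 patients, corresponding to 93 in each group", with no formula.

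The total of 186 recurs in the abstract ("A target sample size of 186 patients") and under Sequence generation, where it is the length of the randomization list.

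**The concern.** An allowance for dropout is meant to ensure that, once the expected share of enrolled patients is lost, the number required by the power calculation is still there. The number to enrol is therefore the required number divided by one minus the dropout rate. Adding 20% to the required number is a different operation and always gives too few, because the later loss is 20% of the larger, enrolled number.

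The total of 93 per arm looks like the product of that second operation. If so, a reader who relies on 90% power with 20% dropout relies on a combination that the planned enrolment does not deliver. There is also no slack: 77 is the smallest whole number per arm that reaches 90% under the named test, so any shortfall below 77 takes power below target.

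**Working it through.** **Inputs** (Sample size section; the 1:1 ratio is also in the abstract): p1 = 0.46, p2 = 0.22, two-sided alpha 0.05 (z = 1.960), target power 90% (z = 1.282), equal arms, unpooled variance, dropout 20%, enrolment 93 per arm.

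**Step 1: reproduce the base sample size.**

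n = (z for alpha + z for power)² × [p1(1 − p1) + p2(1 − p2)] / (p1 − p2)²

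- Variance sum: 0.46 × 0.54 + 0.22 × 0.78 = 0.2484 + 0.1716 = 0.42
- Squared difference: 0.24² = 0.0576
- n = (1.960 + 1.282)² × 0.42 / 0.0576 = 76.6, so 77 per arm

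Power at n per arm is Φ(0.24 / √(0.42 / n) − 1.960). At n = 77 this is Φ(3.250 − 1.960) = 90.14%, close to the printed 90.188%. The base figure stands. A pooled-variance formula would give 80 per arm and a continuity-corrected one 88, so the unpooled test that the protocol names is the one that fits.

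**Step 2: reproduce the enrolment figure.**

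| Inflation | Per arm | Total |
|---|---|---|
| 77 × 1.2 = 92.4 | 93 | 186 (the protocol's figure) |
| 77 / 0.8 = 96.25 | 97 | 194 |

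The protocol prints no formula, so multiplication by 1.2 is an inference, but it gives the printed figure exactly. The next step does not depend on it.

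**Step 3: apply the stated dropout to the stated enrolment.**

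- Remaining per arm: 93 × 0.8 = 74.4, which is 2.6 below 77
- Remaining in total: 186 × 0.8 = 148.8, against 154 required
- Largest dropout that leaves 77 of 93: 1 − 77/93 = 17.2%

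**Step 4: power at what remains, same formula.**

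| Patients per arm | Power |
|---|---|
| 74 | 88.98% |
| 74.4 (unrounded) | 89.15% |
| 75 | 89.38% |
| 76 | 89.77% |
| 77 | 90.14% |

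Two gaps should be kept apart. After 20% dropout the trial is 2.6 patients per arm short of 77, and that gap causes the loss of power. To close it at enrolment would take 97 − 93 = 4 more per arm, 8 in total.

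**The case against.** The strongest counter-argument is that dropouts do not all leave the analysis. The Statistical methods section keeps randomized patients who have an evaluable baseline, at least one dose and at least one evaluable follow-up. It codes non-completers as treatment failures and uses multiple imputation under missing at random. A patient who leaves after week 4 can therefore still be analysed, and the number analysed could be 77 or more per arm even with 20% dropout.

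This stands as a limit on the 89% figure, which treats each dropout as contributing nothing. It does not rescue the sentence in question:

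- The Sample size section discounts for dropouts and takes no credit for imputation. If every dropout counted in full, no allowance would be needed; 93 per arm would give Φ(0.24 / √(0.42 / 93) − 1.960) = 94.6% power.
- An imputed patient carries less information than an observed one, and how much is recovered is not known in advance. It cannot be assumed to make up the difference.
- Failure coding can cost power. Suppose, as an illustration, that 20% in each arm drop out and all count as non-responders in the proportion used for planning. The rates become 0.46 × 0.8 = 0.368 and 0.22 × 0.8 = 0.176, the variance sum is 0.2326 + 0.1450 = 0.3776, and power with 93 per arm is Φ(0.192 / √(0.3776 / 93) − 1.960) = 85.4%.

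Two further objections are fair. The effect is small, about one percentage point. And the power figure being corrected is for a comparison of proportions, whereas the Outcome measures section defines the primary endpoint as a reduction in mean monthly headache days. That is a separate and larger matter; if the base sample size is recalculated for it, 97, 194 and 89% are all superseded. Until then, the printed figures should at least agree with one another.

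**Conclusion.** The concern holds. The required 77 per arm reproduces, but enrolling 93 per arm with 20% dropout leaves about 74, and power on the protocol's own test falls from 90.1% to about 89%. The planned 186 patients support 90% power up to 17.2% dropout, not 20%.

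The conclusion takes 20% to mean a share of enrolled patients, which is the ordinary meaning, and the 89% counts only patients who complete with observed data. The contradiction between 77, 20% and 93 follows from the printed numbers whichever formula was used. It is a certain error of modest size, worth correcting, and it does not threaten the validity of the trial.

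**What to change.** Keep 186 and correct the last sentence of the Sample size section in one of two ways:

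- 186 patients (93 per arm) allow for 17% dropout with 90% power; or
- 186 patients (93 per arm) give about 89% power after 20% dropout.

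The sentence should also say that the power refers to patients with observed outcome data. If the sample size is recalculated for the continuous primary endpoint, divide the new base number by one minus the dropout rate so that the slip is not repeated.

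The cost is one sentence and a slightly less favourable figure. Recruitment, the abstract and the randomization list stay as they are. If the sponsor prefers to hold both 90% power and 20% dropout, enrolment becomes 194, which is 8 more patients, and the total in the abstract, the Sample size section and Sequence generation must change together.

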## Methods: Assignment of interventions

### Allocation

#### Sequence generation

The external block randomization process will take place at Yunnan University. The project statistician will create a randomized treatment allocation schedule using SPSS by generating 186 numbers. Patients who fulfill criteria for enrollment will be randomly assigned to receive gastrodin or placebo according to a centralized randomization schedule in blocks of 4, stratified by gender and headache frequency at baseline (<14 vs. >14 days per month), to achieve between-group balance in the baseline. Subjects will be assigned to the next available medication number within the block.

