## Introduction

### Background and rationale

Medication overuse headache generally refers to monthly headache days of ≥15 per month resulting from acute “medication overuse” (MO) defined as the frequent consumption of acute pain medications above a certain threshold (e.g., 10 or 15 days per month depending on the medication type) for ≥3 months. Diagnostic criteria for MOH were introduced in the International Classification of Headache Disorders, 2nd edition (ICHD-2) (1) without a the requirement of the diagnosis of chronic migraine (CM; see Appendix for details on MOH and CM). In the third edition beta version (ICHD-3β), updated in 2013, concurrent CM and MOH are diagnosed if both criteria are met (2). These criteria remain the same in the ICHD-3 criteria.

The prevalence of MOH is still uncertain (3) and varies from 2% in a recent population-based study (4) to 60% in the Global Burden of Disease Study (5). Whether MOH is a cause or consequence of frequent acute medication intake has been debated for years (6, 7). Nonetheless, MO and MOH management are important in clinical care. MO is associated with an increased risk of chronic headache (8) and chronic migraine (9, 10).

Prognosis of MOH due to different type of chronic headache is probably variable. Although there is evidence that chronic tension-type headache (CTTH) and CM may have partly distinct pathophysiological mechanisms, clinical experience suggests that these two clinical entities may be at opposite poles of a single disease spectrum (11, 12). Of note, CM with MO represents a more severe subgroup of patients and can be difficult to treat (13). In a preplanned subgroup analysis that evaluated efficacy and safety of erenumab in patients with CM and MO, the medication overuse subgroup had a higher proportion of failing to respond to preventive treatment (14).

Effective education for people with MOH plays a major role in effective withdrawal therapy. Successful educational interventions rely largely on a productive doctor-patient alliance (15) and patients' motivation for adherence. In addition, it is often recommended to add a preventive therapy or optimize existing preventive regimens to reduce the number of monthly headache days, improve sense of self efficacy and as a result reduce both the physical and psychological need for acute medication for migraine. Preventive treatments may be pharmacologic, non-pharmacologic, or both.

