### Eligibility criteria

#### Inclusion criteria

Eligible patients are men or women aged 18–70 years with a pre-existing headache disorder onset at or before age 50, fulfilling the ICHD-3 diagnostic criteria for MOH (coded as 8.2) (35) with ≥15 headache days per month and with regular overuse of acute pain medications ≥ 10 or 15 days per month depending on the medication type for ≥ 3 months.

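### The headache-frequency stratification cut (below 14 vs above 14 days) lies under the entry threshold of 15 days, so the factor is inactive if both use the same baseline count

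*Protocol article*

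**What the plan says.** Sequence generation sets out permuted blocks, "according to a centralized randomization schedule in blocks of 4", and the allocation is "stratified by gender and headache frequency at baseline (<14 vs. >14 days per month), to achieve between-group balance in the baseline". The same paragraph limits randomisation to eligible patients: "Patients who fulfill criteria for enrollment will be randomly assigned to receive gastrodin or placebo".

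Inclusion criteria require the ICHD-3 diagnosis "with ≥15 headache days per month and with regular overuse of acute pain medications". Background and rationale uses the same threshold: "Medication overuse headache generally refers to monthly headache days of ≥15 per month".

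Participant timeline says when the baseline count is collected: "During the 28-day screening period, baseline information on demographics, number of monthly headache days" and other measures are gathered for the four weeks before randomisation.

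Outcome measures makes the stratifying variable the baseline of the main comparison: "Primary efficacy endpoint is reduction in the mean number of monthly headache days from baseline at 24-week follow-up". For continuous outcomes, Statistical methods names Student's t-test and the Mann-Whitney test, neither of which adjusts for baseline.

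**The concern.** A stratification factor is useful only if randomised patients can fall on both sides of its cut. Here the cut lies just below the lowest value that the entry criterion allows, so it does not divide the trial population. The two levels also leave a gap, because a patient with exactly 14 days belongs to neither.

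The variable matters. Monthly headache days at baseline is subtracted to form the primary endpoint, and it is the only stratifier named besides gender. The protocol states that stratification is there to balance the arms at baseline. If the factor is inactive, that purpose is not met for this variable, and the tests named in the article would not correct a chance imbalance afterwards.

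**Working it through.** The plan gives no figure for baseline balance, so there is none to reproduce. The sample size is not affected by this point.

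**Step 1. Set the cut against the entry criterion.**
- Eligible: at least 15 headache days per month (Inclusion criteria).
- Baseline window: 28 days (Participant timeline), so the eligible whole-number counts are 15 to 28, which is 28 − 15 + 1 = 14 values.
- Below 14: 0 of these 14 values. Above 14: all 14 of them. Exactly 14: no level.
- Gender by frequency gives 2 × 2 = 4 planned strata. Two are empty, which leaves gender alone.

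**Step 2. Size of the chance imbalance that is left uncontrolled.**
- Input: 93 per arm (Sample size). SD is the between-patient SD of baseline headache days.
- SE of the difference in baseline means = SD × √(1/93 + 1/93) = SD × √(2/93) = 0.147 SD.
- P(|difference| > 0.2 SD) = 2 × [1 − Φ(0.2/0.147)] ≈ 0.17.

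This treats headache days as unrelated to gender. It would hold for any covariate that is not stratified in a trial of this size.

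**Step 3. Illustration in days.** The article gives no distribution of baseline days and no gender split. As assumptions only, take 75% women and counts uniform on 15 to 28. Blocks of 4 were simulated for 186 patients, 6,000 trials per scheme:

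| Stratification | SD of between-arm difference (days) | Chance of a difference above 1 day |
|---|---|---|
| Gender and the documented cut | 0.60 | about 9% |
| Gender only | 0.59 | about 9% |
| Gender and an illustrative cut at 22 or more | 0.30 | about 0.05% |

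The mean difference was about 0 in all three. The first two rows agree within simulation error, as Step 1 requires. A hand check gives the same scale. The SD of a uniform count on 14 values is √[(14² − 1)/12] = 4.03, and 4.03 × 0.147 = 0.59 days. Within each half of 7 values the SD is √[(7² − 1)/12] = 2.0, and 2.0 × 0.147 = 0.29 days.

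**Step 4. Effect on the primary comparison.** Let β be the slope of week-24 headache days on baseline days. In an unadjusted comparison of reductions, a baseline difference D shifts the result by (1 − β) × D, in favour of the arm with the higher baseline. The article does not give β. Over an assumed range of 0 to 1, a D of 0.2 SD shifts the comparison by 0.2 SD down to 0.

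**The case against.** Three stronger readings are tempting, and the document does not support them.

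- **That headache frequency is left unbalanced, or the result biased.** Patients are "randomly assigned to either the gastrodin or placebo group at a ratio of 1:1", which balances every covariate in expectation. Blocked 1:1 allocation within gender is valid. Only the extra protection against chance imbalance is lost.
- **That the lower level is certain to hold none of the 186 patients.** This needs eligibility and stratification to use the same count, and the article does not say that they do. Diagnosis may rest on history, while the stratifier is the count in the 28 days before randomisation. The brief education on medication overuse is also completed before randomisation. A patient diagnosed on history could therefore record fewer than 14 days. However, nothing says that such a patient would be kept, and on the natural reading the level is empty. A month-length conversion does not rescue the cut either: 15 days in 30 becomes 15 × 28/30 = 14.0 days in 28, which has no level.
- **That 186 numbers in blocks of 4 imply one unstratified list.** The text says that the blocks are stratified, and an incomplete last block is routine.

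Two further objections stand in part. The 17% is generic, and the figures in days rest on assumed distributions, so neither predicts harm to this trial's result. The endpoint is already a reduction from baseline. Step 4 shows that this removes the effect of an imbalance only if β is 1. Finally, the analysis plan is not shown and may already adjust for baseline, so the lack of an adjusted model in the article is not itself a fault. Adjustment appears below only as a remedy.

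**Conclusion.** The contradiction holds as an inconsistency between Sequence generation and Inclusion criteria, and no other section of the article repairs it. Provided that eligibility and stratification use the same baseline count, the frequency factor is inactive and the scheme stratifies by gender alone. The stated aim of baseline balance then gets no help from stratification on the variable that feeds the primary endpoint.

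The consequence is moderate: about a one-in-six chance of a baseline difference above 0.2 SD, which a working factor would reduce. There is no bias, no inflation of the type I error and no change in the required number of patients. Severity: should be fixed.

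**What to change.** Reconcile the two sections by one of two routes.

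1. **If no patient has been randomised:** replace the cut with one inside the eligible range (15 days or more) and without a gap, so that every eligible count belongs to exactly one level. Set it near the median that the sponsor expects; the article gives no distribution from which to choose a value. State that the stratifier is the 28-day baseline count, and generate the blocks of 4 within each gender-by-frequency stratum.
2. **As an alternative, or if recruitment has begun:** drop the frequency factor, and pre-specify before unblinding a primary analysis adjusted for continuous baseline headache days, in place of the unadjusted t-test or Mann-Whitney test. This route may well be the relevant one, because Participant timeline starts enrolment in January 2023 and the article appeared in February 2023. The existing list need not be regenerated: if the factor is inactive, dropping it changes no allocation.

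The first route costs a short amendment and a new list. The second costs a short amendment and a sentence in the analysis plan. Neither needs extra patients.
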